## Abstract

**Introduction::**

End stage renal failure patients on hemodialysis have significant vascular calcification This is postulated to be related to sub-clinical vitamin K deficiency, which is prevalent in hemodialysis patients. Vitamin K deficiency result in the failure of the matrix GLA protein (MGP) to undergo carboxylation. MGP is a natural local inhibitor of vascular calcification and the lack of functional carboxylated MGP may contribute to increase vascular calcification. Vitamin K supplement should therefore correct this anomaly and decrease the rate or severity of vascular calcification in this population of patients on long-term maintenance hemodialysis. Our study seeks to evaluate the prevalence and the progression of vascular calcification in a cohort of maintenance hemodialysis patients. It will also evaluate the efficacy of vitamin K supplementation in reducing the progression of vascular calcification in this group of patients.

**Methods::**

This will be a single-center randomized, prospective and open-label interventional clinical trial of end stage renal failure patients on hemodialysis. We aim to recruit 200 patients. Eligible patients will be randomized to either the standard care arm or active treatment arm. Active treatment arm patients will receive standard care plus supplementation with oral vitamin K2 isoform 360 mcg 3 times weekly for a total duration of 18 months. Primary outcome measured will be absolute difference in coronary artery calcification score at 18-month between control and intervention arms. Secondary outcomes will be to compare absolute difference in aortic valve calcification, percentage of patients with regression of coronary artery calcification of at least 10%, absolute difference in aortic and systemic arterial stiffness, mortality from any cause and major adverse cardiovascular over the same period.

**Discussion::**

Evidence of successful regression or retardation of vascular calcification will support the conduct of larger and longer-term trials aimed at reducing cardiovascular disease mortality and major adverse cardiovascular events in this high-risk population using a safe and inexpensive strategy

**Trial registration::**

ClinicalTrials.gov NCT02870829. Registered on 17 August 2016 – Retrospectively registered, https://clinicaltrials.gov/ct2/show/NCT02870829

National University Hospital's Institutional Review Board (2015/01000)

## Introduction

1

It is well recognized that coronary artery calcification (CAC), a form of vascular calcification (VC), occurs at a much higher rate in the dialysis population compared to age-matched populations without chronic kidney disease (CKD).^[1,2]^ Studies have also confirmed a positive association of CAC with adverse outcomes in this population.^[2]^ There is a dose relationship reported between the CAC score and cardiovascular disease (CVD) mortality; the higher the score, the higher the mortality risk.^[3]^ Given that one major cause of death and hospitalization in the dialysis population is CVD, these observations may be of critical importance in efforts to reduce CVD mortality and morbidity.^[2]^

Two distinct types of VC are reported in the CKD population.^[4]^ Atherosclerotic calcification occurs in the intimal layer and is associated with atherosclerosis and potentially rupture of unstable plaque, leading to acute myocardium infarction and stroke. Various animal models and human studies support the development of this form of VC in uremic and non-uremic settings. Another form, medial calcification (calcific arteriosclerosis) is also commonly observed in CKD and uremia, and contributes to a higher CVD mortality in this population due to increased vascular stiffness with loss of vessel elasticity, resulting in increased cardiac afterload, progressive left ventricular hypertrophy and ultimately, heart failure and arrhythmia.^[5]^

In the general non-CKD population, established risk factors for CAC are older age, diabetes, hypertension, dyslipidemia and smoking, while in CKD, dialysis vintage is an additional risk factor.^[6]^ Several factors unique to the uremic population appear to increase the risk of medial calcification which differs in pathogenesis from intimal atherosclerotic calcification, being typically non-inflammatory in nature.^[7]^ Hyperphosphatemia, elevated calcium-phosphate product and use of calcium-containing phosphate binders (a reflection of excess calcium loading) have been associated with an increased risk of VC in the CKD population. 1,25 (OH)2 Vitamin D3 supplementation, commonly employed to suppress parathyroid hormone in CKD, has also been implicated as a cause of VC.^[8]^ Other promoters (such as bone morphogenetic protein and osteocalcin) and inhibitors (such as matrix Gla protein and fetuin-A) of VC have been identified.^[9–12]^ While their role in clinical management remains to be established, these proteins are potential therapeutic targets in CKD-associated VC.

Given that CVD is a major cause of mortality and morbidity in the CKD population, there has been intense interest in therapies to reduce CVD events. Statin therapy has proven very successful in reducing major adverse cardiac events (MACE). However, two large prospective randomized controlled trials could not demonstrate a significant reduction in CVD, non-fatal myocardial infarction and non-fatal stroke in patients on hemodialysis assigned to potent hypolipidemic agents (namely atorvastatin and rosuvastatin) despite significant LDL-cholesterol lowering compared to placebo.^[13,14]^ Control of other CVD risk factors which can accelerate VC is routine in the management of patients on dialysis. However, there are no randomized trials investigating the effect of glycemic or blood pressure control on VC or CAC in this population.

The latest frontier in the battle against VC and CVD in the dialysis population is CKD-mineral bone disorder which is characterized by excessive calcium loading, phosphate retention and hyperparathyroidism.^[15]^ In vitro as well as population studies support the role of each of these factors, alone or in combination, in the genesis of VC.^[16,17]^ Therefore, efforts to reduce VC in the CKD population have focused on correcting the altered bone mineral homeostasis. Reduction in calcium load is achieved by using lower dialysate calcium concentrations and non-calcium containing phosphate binders such as sevelamer.^[18,19]^ Lowering of serum phosphate in CKD patients with elevated phosphate level is also key to reducing the onset and severity of VC. There has been some success with the use of calcimimetics in reversing VC in dialysis patients.^[20]^ However, the largest randomized controlled trial to date did not show a statistically significant reduction in CVD outcomes in hemodialysis patients with moderate to severe hyperparathyroidism receiving cinacalcet over a median of 21 months compared to placebo.^[21]^

The cellular and molecular events leading to calcium deposition in vascular tissue are highly regulated. Animal and molecular studies have demonstrated that vitamin K can influence the development and progression of VC, via its involvement in the carboxylation of matrix GLA protein (MGP).^[22,23]^ MGP, a protein synthesized by vascular smooth muscle cells, functions as a natural local inhibitor of VC^[24,25]^ but becomes functional only after vitamin K2-dependent carboxylation. MGP deficient mice have been shown to develop massive calcification and do not survive beyond 6 weeks of birth.^[26]^ Many dialysis patients may have sub-clinical vitamin K deficiency, possibly related to dietary restriction, as evidenced by the high level of dephosphorylated undercarboxylated MGP (dp-ucMGP) measured in this population.^[27]^

Oral vitamin K supplementation can enhance carboxylation of MGP and lower plasma dp-ucMGP. Vitamin K1 (phylloquinone) is the usual dietary source of vitamin K. Vitamin K2 is derived from enterocyte conversion of vitamin K1 or from indigenous gut bacteria production^[28]^ although 1 food source, natto (soybean fermented using Bacillus subtilis) has a very high content of vitamin K2.^[29]^ The precise dose of vitamin K needed in the physiological state to activate all vitamin K dependent proteins is not entirely clear. There is also an inherent divergent use of vitamin K1 for carboxylation of vitamin K dependent proteins in the liver such as for coagulation factors, preferentially over its utilization in the periphery (extra-hepatic), as a mean of ensuring adequacy of certain essential protein function for short-term survival.^[30]^ This preferential triaging of the utilization of vitamin K may result in significant reduction of vitamin-K dependent carboxylation of extra-hepatic vitamin-K proteins even when modest deficiency exists. Peripheral carboxylation of vitamin K dependent proteins such as MGP are dependent on long-chain isoforms of vitamin K2 (menaquinones). One such isoform with proven efficacy in decreasing dp-ucMGP levels is menaquinone-7 (MK-7).^[27]^

A recent randomized trial reporting 1-year outcome of vitamin K2 supplementation in hemodialysis patients found no effect on aortic calcification despite reduction in dp-ucMGP.^[31]^ There are still two ongoing trials evaluating the impact of vitamin K1 supplementation on VC in end stage renal failure (ESRF) and 1 with vitamin K2 supplementation in ESRF patients with non- valvular atrial fibrillation.^[32–34]^ All these trials were conducted in the Caucasian populations. As vitamin K intake will vary according to diet, there may well be differences between European and North American patient groups compared to those from Asia. To our knowledge, there are no similar studies in Asians. The proposed “Treatment to Reduce Vascular Calcification in Hemodialysis Patients Using Vitamin K” (Trevasc-HDK) study is therefore timely.

## Objectives

2

The primary objective of Trevasc-HDK is to evaluate the effect of vitamin K2 (MK-7) supplementation on the progression of CAC in ESRF patients on HD. We hypothesize that oral MK-7 will enhance carboxylation of MGP, lower levels of dp-ucMGP and reduce CAC and/or aortic vascular calcification (AVC) in the HD population. Secondary outcomes of interest include the effects of MK-7 on AVC (known to be correlated with CAC), aortic stiffness (which is determined by aortic calcification rather than atherosclerotic plaque burden) and clinical outcomes (see “Study outcomes” below). Trevasc-HDK will also provide the first local data on the prevalence and severity of CAC or AVC in patients on maintenance HD, as well as the natural history of calcification in those not receiving MK-7.

## Methods

3

**Study design** Trevasc-HDK is a single-center randomized, prospective and open-label interventional clinical trial of ESRF patients on HD. The study protocol was developed in adherence to the Good Clinical Practice Guidelines and Standard Protocol Items: Recommendations for Intervention Trials.^[35]^ The study is performed according to the ethical standards of the National University Hospital's Institutional Review Board (2015/01000) on clinical trials with human subjects and with the Helsinki Declaration of 1975 (and as revised in1983). The trial is registered at ClinicalTrials.gov (NCT02870829).

### Study setting:

3.1

National University Hospital is 1 of the major academic tertiary hospitals in Singapore caring for ESRF patients. Potential study subjects are identified from the Haemodialysis and Nephrology clinics in this hospital (single site). All patients will continue to receive standard of care dialysis at their usual satellite dialysis units during the conduct of this study.

### Eligibility criteria:

3.2

Patients meeting the inclusion and exclusion criteria will be invited to participate and written informed consent obtained for those willing to participate. Consented subjects will attend a screening visit (V0) where a multislice computed tomogram will be performed to assess their degree of CAC. As the main objective is to investigate the effects of intervention on VC, pre-existing CAC indicated by a baseline CAC score of ≥ 30 Agatston units is mandated for entry into the trial. This threshold also excludes patients with mild CAC which is unlikely to progress in the relatively short window of observation.^[19]^ Other inclusion and exclusion criteria are outlined in Table 1. Consent is taken by study team co- investigator after detailed explanation of purpose, benefit and risk of the study. Witness is required for patient signing informed consent in Chinese and Malay language. Patients are informed the right to withdraw consent and participation at any time during the study period.

**Table 1 T1:**
[figure not shown]
Inclusion and exclusion criteria.

### Study interventions

3.3

Eligible patients will be randomized to either the control arm (standard care) or active treatment arm (standard care plus supplementation with vitamin K2 isoform MK-7). The dose of MK-7 chosen is oral 360 mcg 3 times weekly for a total duration of 18 months.

Patients will be randomly allocated into control and intervention arms in a 1:1 fashion using random permuted blocks of size 4 and 6. The randomization will be stratified by diabetes status. The sequence of treatment allocation will be generated using the *ralloc* module of the STATA software. Randomization will be performed by clinical trial unit coordinator during office hour.

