### Sample size

3.4

To ensure that the study is adequately powered, we have estimated the sample size based on the primary outcome of absolute difference in CAC score at 18-months between the control and intervention arms, assuming mean CAC scores at 18-months of 1005 and 786 respectively as reported by Block et al.^[19]^ Applying natural logarithmic transformation to CAC scores due to skewed distribution, this corresponds to a mean logCAC of 6.91 and 6.67, respectively. Further assuming a common SD of 0.55, power of 80%, 2-sided level of significance of 5% and equal allocation between the 2 treatment arms, a minimum sample size of 170 in total, or 85 per arm will be required. Accounting for an attrition rate of 15%, we will recruit a total of 200 patients.

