### Statistical methods

3.9

The absolute difference in CAC and AVC scores at 18-months between control and intervention arms will be compared using the t-test following log transformation. Adjustment for baseline CAC and AVC scores respectively will be made via the analysis of covariance. Likewise, the effects of MK-7 supplementation on dp-ucMGP level, CFPWV and AI at 18 months will be compared between the 2 groups using the t-test, with adjustment made for the respective baseline covariates via analysis of covariance.

The percentage of patients with regression of CAC score of ≥ 10% at 18 months from baseline will be compared between control and intervention arms via the χ^2^ test. The effect of treatment will be quantified using the odds ratio estimate and its associated 95% confidence interval. The logistic regression analysis will be used to account for potential confounders where applicable.

For all-cause mortality and MACE, the time to the respective event is defined as the time from randomization to the time when the event of interest occurred. Subjects in whom an event was not observed will be censored at 18-months. The Kaplan-Meier survival analysis and the log-rank test will be used to compare the survival distributions between the control and intervention groups. The effect of treatment will be quantified using the hazard ratio estimate and its associated 95% confidence interval. Further, the Cox proportional hazards regression stratified by diabetes will be used to account for potential confounders where applicable.

All statistical evaluations will be made assuming a 2-sided test at the 5% level of significance based on an intention-to-treat analysis.

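### Diabetes stratifies the randomization but is left out of the t-test, ANCOVA, chi-square and log-rank analyses: a small, conservative loss of efficiency that is nearly free to correct

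*Protocol article*

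**What the plan says.** Under Study interventions, patients are allocated "in a 1:1 fashion using random permuted blocks of size 4 and 6", and "The randomization will be stratified by diabetes status". Diabetes is the only stratification factor.

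Under Statistical methods, the planned analyses are:

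- **CAC and AVC at 18 months:** a t-test on log-transformed scores, then "Adjustment for baseline CAC and AVC scores respectively will be made via the analysis of covariance". The same pair of methods is used for dp-ucMGP, cfPWV and AI, each with its own baseline value as covariate.
- **CAC regression of at least 10%:** a chi-square test, with logistic regression for unnamed confounders if judged applicable.
- **Mortality and MACE:** "The Kaplan-Meier survival analysis and the log-rank test will be used to compare the survival distributions between the control and intervention groups". The section then adds: "Further, the Cox proportional hazards regression stratified by diabetes will be used to account for potential confounders where applicable".

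So the stratum appears in one analysis only, and that analysis is optional.

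**The concern.** Permuted blocks within diabetes strata hold the proportion of diabetic patients nearly equal between the arms. If diabetes predicts the outcome, this removes the between-stratum variation from the treatment contrast. An analysis without the stratum still counts that variation in its standard error. The interval is then wider and the p-value larger than the design warrants, so the precision bought by stratifying goes unused.

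The authors evidently expect diabetes to matter. They stratify on it, and the Introduction lists it among the established CAC risk factors, although for the general population without CKD. The section names the ANCOVA covariates and stratifies the Cox model, so leaving diabetes out of the other analyses reads as a choice the article makes and not as detail it leaves open.

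**Working it through.** **Inputs from the article (Sample size).** "this corresponds to a mean logCAC of 6.91 and 6.67, respectively", a difference of 0.24. "Further assuming a common SD of 0.55". "power of 80%, 2-sided level of significance of 5% and equal allocation between the 2 treatment arms". 85 evaluable per arm; 200 recruited to allow for 15% attrition.

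**Inputs not in the article (assumed).** The share R² of 18-month log CAC variance explained by diabetes: 0.02 to 0.20. For the ANCOVA check: 50% diabetic, within-stratum correlation 0.7 between baseline and 18-month log CAC, and the same diabetes difference at both visits.

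**Step 1: the plan's own figure.** n per arm = 2 × (1.960 + 0.842)² × 0.55² / 0.24² = 82.4, so 83 (166 in total). The exact t-test needs 84 (168). The stated 170 is within 3%, and 170 / 0.85 = 200. At 85 per arm the SE is 0.55 × √(2/85) = 0.0844, and power is Φ(0.24/0.0844 − 1.960) = 81.2%. The calculation is for an unadjusted comparison and takes no credit for stratification or baseline adjustment.

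**Step 2: the t-test without the stratum.** With 0.55 as the overall SD and near-exact balance within strata, the true SE is 0.0844 × √(1 − R²), while the t-test still uses 0.0844.

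- SE overstatement: 1/√(1 − R²)
- True alpha: 2 × [1 − Φ(1.960/√(1 − R²))]
- Power without stratum: Φ((0.24 − 1.960 × 0.0844) / (0.0844 × √(1 − R²)))
- Power with stratum: Φ(0.24 / (0.0844 × √(1 − R²)) − 1.960)

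| R² | SE overstated | True alpha | Power without | Power with | Points forgone |
|---|---|---|---|---|---|
| 0.02 | 1.0% | 0.048 | 81.4% | 82.0% | 0.5 |
| 0.05 | 2.6% | 0.044 | 81.8% | 83.1% | 1.3 |
| 0.10 | 5.4% | 0.039 | 82.5% | 85.1% | 2.6 |
| 0.20 | 11.8% | 0.028 | 83.9% | 88.9% | 5.0 |

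**Step 3: check by simulation.** Stratified blocks of 4 and 6 with 170 patients and 6,000 trials per setting gave a t-test alpha of 0.052, 0.046, 0.037 and 0.032 for the four rows. The Monte Carlo SE is about √(0.05 × 0.95/6000) = 0.003, so these agree with the formula.

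**Step 4: the baseline-adjusted ANCOVA.** In the same simulation, type I error was 0.048 to 0.055 without diabetes and 0.050 to 0.054 with it. Power changed by about 0.1 point at most (for example 98.6% against 98.7% at R² = 0.10). Power this near its ceiling can hide a gain, so the residual variance is the better guide. At R² = 0.20, as a share of the total:

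- Slope on baseline: 0.7 × 0.8 + 0.2 = 0.76
- Residual variance without diabetes: 1 − 0.76² = 0.4224
- Residual variance with diabetes: 0.8 × (1 − 0.7²) = 0.408
- Ratio of SEs: √(0.4224/0.408) = 1.017

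Even at the top of the range the ANCOVA's SE would shrink by only about 1.7%, because baseline CAC already carries most of the diabetes signal.

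**Not quantified.** No size was computed for the chi-square or log-rank tests. The article gives no event or regression rates from which to do so.

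**The case against.** The strongest case against acting is that little is at stake. The error has one direction only, so no false positive is created. The article gives no effect size for diabetes, its risk-factor statement concerns people without CKD, and at R² = 0.02 the effect is immaterial. Covariate lists and stratified versions of tests are often left to an analysis plan, and the logistic model leaves room for diabetes. Most of this stands and limits the point to a minor one. It does not remove the point: the ANCOVA covariate is named, and the Cox model shows the authors had the stratum in mind.

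A reader might infer three stronger things that the document does not support.

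- **That the trial loses its planned power.** This follows only if 0.55 is a within-stratum SD. With 50% diabetic and a diabetes shift of 1.0 such SD, the overall SD would be 0.55 × √1.25 = 0.615, the t-test's SE 0.0943, and its power Φ((0.24 − 1.960 × 0.0943)/0.0844) = 74%. The Sample size section gives 0.55 as a common SD for a plain two-arm comparison, which is most naturally the overall SD; power then stays above 80%.
- **That the ANCOVA is materially miscalibrated.** Step 4 shows it is not, under the assumptions used.
- **That the log-rank p-value and the stratified Cox hazard ratio conflict.** The stratified Cox model is introduced as an additional analysis, so the article does not present it as the estimate belonging to the log-rank test.

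**Conclusion.** The mismatch between randomization and analysis is real and its consequence is small. If diabetes is prognostic, the unadjusted t-test is conservative: for R² of 0.02 to 0.20 its SE is about 1% to 12% too large, its true alpha about 0.048 to 0.028, and 0.5 to 5 points of available power are forgone. These figures rest on the assumed R² and on 0.55 being the overall SD, in which case planned power is kept. For the baseline-adjusted ANCOVA the gain is close to nil, and it would grow only if diabetes predicts progression beyond what baseline CAC already tells. This is an efficiency and consistency improvement and no threat to validity.

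**What to change.** - **ANCOVAs (CAC, AVC, dp-ucMGP, cfPWV, AI):** add diabetes as a fixed effect. Name the CAC and AVC ANCOVA on log scores as the main comparison in place of the t-test.
- **CAC regression of at least 10%:** use a Cochran-Mantel-Haenszel test stratified by diabetes, or logistic regression that includes diabetes.
- **Mortality and MACE:** stratify the log-rank test by diabetes and report the diabetes-stratified Cox hazard ratio with it.

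The cost is one degree of freedom per ANCOVA and a few lines of analysis-plan wording; the stratum is known for every randomized patient. The odds and hazard ratios become conditional on diabetes, which the plan should say, and their intervals need not be narrower. Study status reports all final visits complete and biomarker analysis pending in an open-label trial, so the change should be written down and dated before the arms are compared.
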